## Abstract

**Background:**

Left ventricular dysfunction and the development of heart failure is a frequent and serious complication of myocardial infarction. Recent animal experimental studies suggested that metformin treatment reduces myocardial injury and preserves cardiac function in non-diabetic rats after experimental myocardial infarction. We will study the efficacy of metformin with the aim to preserve left ventricular ejection fraction in non-diabetic patients presenting with ST elevation myocardial infarction (STEMI).

**Methods:**

The Glycometabolic Intervention as adjunct to Primary percutaneous intervention in ST elevation myocardial infarction (GIPS)-III trial is a prospective, single center, double blind, randomized, placebo-controlled trial. Three-hundred-and-fifty patients, without diabetes, requiring primary percutaneous coronary intervention (PCI) for STEMI will be randomized to metformin 500 mg twice daily or placebo treatment and will undergo magnetic resonance imaging (MRI) after 4 months. Major exclusion criteria were prior myocardial infarction and severe renal dysfunction. The primary efficacy parameter is left ventricular ejection fraction 4 months after randomization. Secondary and tertiary efficacy parameters include major adverse cardiac events, new onset diabetes and glycometabolic parameters, and echocardiographic diastolic function. Safety parameters include renal function deterioration and lactic acidosis.

**Conclusions:**

The GIPS-III trial will evaluate the efficacy of metformin treatment to preserve left ventricular ejection fraction in STEMI patients without diabetes.

## Background

Primary percutaneous coronary intervention (PCI) reduces early mortality and improves late clinical outcome in patients with acute myocardial infarction (MI). Large MI size and adverse left ventricular remodeling may cause post infarct deterioration of left ventricular function and development of overt heart failure.

Metformin, a biguanide oral antihyperglycemic agent used widely for the treatment of patients with type 2 diabetes mellitus, enhances glucose control through increased glucose utilization and decreased endogenous glucose release [1, 2]. Several studies in patients with diabetes demonstrated that metformin is associated with improved outcome and considered to be safe (Table 1) [3–9]. Furthermore, in patients at high risk of developing diabetes, metformin reduced the incidence of diabetes [10, 11].

**Table 1 Tab1:** Effects of metformin on prognosis. RCT: randomized controlled trial; BMI: Body Mass Index; STEMI: ST-elevation myocardial infarction; HR: hazard ratio; OR: odds ratio

Ref.	Subjects	Study design	Number of subjects	Median follow-up	Effect of metformin on blood glucose levels	Effect of metformin on endpoints
3	Obese (BMI >27 kg/m^2^) patients with diabetes	Post-hoc analysis of RCT	753	10.7 years	Comparable to other strategies	Improved survival (*p* = 0.021)
4	STEMI patients with diabetes	Post-hoc analysis of RCT	1,145	4.1 years	Comparable to other strategies	Improved survival (HR death: 0.65, 0.47–0.90, *p* = 0.01)
5	Patients with diabetes undergoing coronary intervention	Post-hoc analysis of RCT	2,772	9 months	Higher blood glucose levels compared to other strategies	Improved survival (OR death: 0.41, 0.21–0.79, *p* = 0.008)
						Lower rates of MI (OR MI: 0.41, 0.20–0.84, *p* = 0.016)
6	Patients with diabetes and atherothrombosis	Observational	19,691	2 years	Higher blood glucose levels compared to other strategies	Improved survival (HR death: 0.76, 0.65–0.89, *p* < 0.001)
7	Elderly patients with diabetes and heart failure	Retrospective	16,417	1 year	No data on glycemic control	Improved survival (HR death: 0.86, 0.78–0.97)
8	Patients with diabetes and heart failure	Observational	6,185	2 years	No data on glycemic control	Improved survival (HR death: 0.76, 0.63–0.92, *p* < 0.001)
9	Patients with type 2 diabetes	Meta-analysis	96,295	1.3 years	No data on glycemic control	No increased risk for lactic acidosis
						No differences in lactate levels

Several preclinical studies in non-diabetic animals reported that metformin may confer cardioprotection by limiting MI size and preventing adverse remodeling. Recently, our group demonstrated that metformin reduces infarct size by 22 % in an experimental non-diabetic rat model of MI, resulting in a relative improvement in left ventricular ejection fraction (LVEF) of 52 % compared to placebo (Fig. 1) [12]. These effects were independent from glycemic control, as these were non-diabetic normoglycemic rats [12]. Other groups confirmed these results in murine and canine models, demonstrating metformin treatment compared to placebo reduced MI size between 22 % to 58 % [13–17], and resulted in a relative improvement in LVEF between 31 and 52 % [13, 14].

**Fig. 1 Fig1:**
[figure not shown]
metformin resulted in a relative improvement in left ventricular ejection fraction of 52 % compared to placebo. MI: myocardial infarction; **P* < 0.05 vs. sham group; # *P* < 0.05 vs. placebo group. Adapted with permission from: Fig. 2 from Meimei Yin, [name], Joost P van Melle, Cheng Qian, Wiek H van Gilst, Herman HW Silljé, and [name]. Metformin improves cardiac function in a nondiabetic rat model of post-MI heart failure. Am J Physiol Heart Circ Physiol August 2011 301:(2) H459–H468

Current medical strategies are predominantly aimed at establishing reperfusion and secondary prevention including prevention of thrombo-embolism and inhibition of the renin-angiotensin system. Reducing infarct size and positive cardiac remodeling by metformin therapy provides a potential novel strategy to preserve functional myocardium and thereby improve prognosis.

## Mechanism of action and potential benefit

Effects of metformin include decreased hyperglycemia, hypoinsulinemia, higher peripheral muscle glucose uptake, decreased hepatic glyconeogenesis, reduced hypercoagulability, improvement of the lipid profile, nitric oxide mediated vasodilatation, and additional cardioprotective effects [1]. Reported cardioprotective effects of metformin include attenuation of myocardial infarct size and improved left ventricular function. The exact mechanisms of action that explain these numerous effects of metformin remain to be elucidated. Especially our understanding of the cardioprotective effects of metformin, beyond glucose lowering, is incomplete [18]. Several ancillary mechanisms have been proposed to explain metformin induced cardioprotection, these are displayed in detail in Fig. 2 [12–33].

**Fig. 2 Fig2:**
[figure not shown]
visualization of the proposed cardioprotective mechanism of action of metformin in the human heart after myocardial infarction, resulting in improved systolic and diastolic function. In experimental models metformin has been consistently associated with enhanced phosphorylation of AMP activated protein kinase (AMPK) [12–24]. In the myocardium, characterized by high energy demands and low energy reserves, AMPK plays a pivotal role in maintaining metabolic homeostasis [18–21]. Metformin-induced AMPK phosphorylation may be mediated by inhibition of complex 1 of the respiratory chain, by upstream activation of the tumor suppressor gene liver kinase B1 (LKB1), or by decreased AMP–deaminase activity [21–24]. AMPK phosphorylation leads to activation of the Reperfusion Injury Salvage Kinase (RISK) pathway including phospatidylinositol-3-kinase (PI3K) and Akt pathways [17, 26], upregulation of the tumor suppressor gene p53 [27], inhibition of mammalian target of rapamycin (mTOR) [19], and upregulation of endothelial nitric oxide synthase (eNOS) [1, 13]. Activation of the RISK pathway and eNOS improves mitochondrial function and inhibits opening of the mitochondrial permeability transition pore (mPTP) [26]. The mPTP is a major mediator of myocardial reperfusion injury. Opening of the mPTP results in ATP depletion and cell death [25, 26]. Further, prevention of mPTP opening stimulates mitochondrial respiration, improving ATP availability and cellular function [25]. Upregulated p53 and inhibited mTOR, partly RISK pathway mediated, are associated with decreased cellular vulnerability by preventing post-mitotic cell death and improved resilience to ischemia related injury [19, 27]. Metformin mediated eNOS production, next to increasing nitric oxide production, enhances sodium pump activity causing decreased intracellular calcium levels [1]. In infarcted tissue, this may attenuate microvascular obstruction and thereby prevent mPTP mediated cell death [28]. In functional myocardium, optimized calcium handling results in improved contractility and relaxation [1]. Further, independent of AMPK, metformin inhibits transforming growth factor (TGF)-β1 myocardial expression, decreasing collagen synthesis and preventing fibrosis [29]. Metformin may also attenuate cardiac fibrosis by directly inhibiting advanced glycation endproduct (AGE) formation [30]. Also, metformin is associated with a decrease in dipeptidyl peptidase-4 activity and an increase in circulating levels of glucagon-like peptide 1 [31]. In a porcine model of ischemia and reperfusion injury, stimulation with a analogue (exenatide) resulted in a reduction of infarct size [32]. Another target of metformin may be the increase of glucose utilisation of the heart. The adult heart mainly relies on fatty acids utilisation, and switches back to glucose when damaged. However, metabolic flexibility of the failing heart is limited, and facilitation of glucose utilisation by metformin via increase of glucose transporters (GLUT-1 and GLUT-4) may explain its salutary effects on the cardiac function [12, 33]

Collectively, the metformin induced changes in myocardial gene and energy program, especially the activation of AMPK, are associated with decreased infarct size, prevention of adverse remodeling, and result ultimately in improved cardiac function.

## Study design

The GIPS-III trial is a single center, prospective, double-blind, randomized, placebo-controlled trial, designed to evaluate the efficacy of a 4 month metformin treatment on preservation of LVEF in non-diabetic STEMI patients requiring primary PCI treatment. A total of 350 non-diabetic STEMI patients will be included in the GIPS-III trial.

### Eligibility

In- and exclusion criteria are listed in Table 2. In brief, subjects presenting with an acute STEMI treated with primary PCI, including the implantation of at least 1 stent with a diameter of at least 3.0 mm are considered for this trial. Verbal followed by written informed consent will be required from each patient.

**Table 2 Tab2:** In- and exclusion criteria for the GIPS-III trial. MI: myocardial infarction; ECG: electrocardiogram; PCI: percutaneous coronary intervention; MRI: magnetic resonance imaging

Inclusion criteria	Exclusion criteria
• The diagnosis acute MI defined by chest pain suggestive for myocardial ischemia for at least 30 min, the time from onset of the symptoms less than 12 h before hospital admission, and an ECG recording with ST- segment elevation of more than 0.1 mV in 2 or more leads	• Prior MI
	• Diabetes
	• Creatinin >177 μmol/L measured pre-PCI
	• Need for coronary artery bypass grafting
	• Rescue PCI after thrombolytic therapy
• Successful primary PCI <12 h from onset of symptoms	• When subjects develop a condition which, in the investigator’s judgment, precludes study therapy
• Verbal followed by written informed consent	• Inability to provide informed consent
• At least one stent sized ≥3.0 mm	• Younger than 18 years
• Eligible for cardiac MRI-scan:	• Contra-indication to metformin
- Body Mass Index <40 kg/m^2^	• an estimated life-expectancy of less than 6 months
- no ferromagnetic metal objects in the body	
- no claustrophobia	

### Treatment

All patients will receive standard medical treatment for a STEMI according to European practice guidelines [34].

The flow chart of the GIPS-III trial is shown in Fig. 3. During the primary PCI procedure witnessed verbal informed consent will be obtained by the interventional cardiologist and additional blood samples will be drawn for storage. As soon as possible, but no more than 3 h after successful PCI, patients will be randomly assigned to a 4 month treatment with white film-coated tablets containing metformin hydrochloride 500 mg or visually matching placebo, administered twice daily. Secondary prevention will according to ESC guidelines include aspirin, thienopyridines, statins, angiotensin converting enzyme (ACE) inhibitors, and beta-receptor blockers, when indicated and tolerated [34, 35].

**Fig. 3 Fig3:**
[figure not shown]
Flow chart of the GIPS-III trial. STEMI, ST-elevation myocardial infarction; PCI, percutaneous coronary intervention; LVEF, left ventricular ejection fraction; MRI magnetic resonance imaging; OGTT oral glucose tolerance testing

Subjects are scheduled for return visits at 2 weeks, 2 months, 4 months, and 12 months after hospital discharge. During every visit examination, assessment of clinical events and 12-lead electrocardiography are performed. During the 4 month visit the amount of study drug received, dispensed, and consumed will be recorded.

Study drug treatment will be discontinued in the following situations: 1) when subject withdraw consent, 2) in case of pregnancy, 3) when subjects develop severe renal dysfunction (defined as creatinin >177 μmol/L, or an estimated GFR <30 ml/min*1.73 m^2^), or 4) when subjects develop a condition which, in the investigator’s judgment, precludes further therapy. Discontinuation will have no consequence for the regular patient care. Since metformin therapy used as a single antihyperglycemic drug is not associated with hypoglycemia and due to the blinded nature of this trial, there will be no dose modifications of the study medication.

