### Laboratory analysis

During hospitalization, blood will be sampled at baseline and at 3, 6, 9, 12, and 24 h after PCI to monitor values of cardiac enzymes and high sensitive troponin [39]. Less frequently during hospitalization and at every visit to the outpatient clinic hemoglobin, platelets, glucose, creatinin and liver enzymes, total cholesterol, high-density and low-density lipoprotein, and N-terminal pro B-type natriuretic peptide will be determined.

Furthermore, during PCI, 24 h after PCI, and at every visit to the outpatient clinic, blood samples for additional analyses will be collected [40]. These analyses will include, but are not limited to, glycometabolic determinants, biomarkers, and other markers of disease severity or relevant to the disease [41, 42].

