## Current status

The GIPS-III trial has been approved by the local institutional review board, national regulatory agencies, and is being carried out according the Declaration of Helsinki (Seoul 2008). GIPS-III has enrolled its first patient in January 2011. As of August 1st, 2012, 266 patients have been randomized. Completion of the inclusion is anticipated in January 2013. Primary endpoint analysis of the final randomized patient is expected in April 2013.

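### The numeric renal exclusion (creatinine above 177 μmol/L) omits the eGFR below 30 limb of the stopping rule, so a patient could be randomised already past the stopping threshold

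*Protocol article*

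**What the plan says.** The Treatment section lists four reasons to discontinue study drug. The third applies "when subjects develop severe renal dysfunction (defined as creatinin >177 μmol/L, or an estimated GFR <30" ml/min per 1.73 m². Either limb is enough.

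Table 2 (Eligibility) has one numeric renal exclusion: "Creatinin >177 μmol/L measured pre-PCI". It contains no eGFR value. Two general exclusions in the same table could bear on renal function: "Contra-indication to metformin", and a condition that in the investigator's judgment "precludes study therapy". Neither names a renal threshold.

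The abstract summarises the exclusions as follows: "Major exclusion criteria were prior myocardial infarction and severe renal dysfunction". It does not define severe renal dysfunction. The only definition in the article is the two-limb one in the stopping rule.

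On timing, the Treatment section says that "no more than 3 h after successful PCI, patients will be randomly assigned" to study drug. Later renal monitoring is described under Laboratory analysis: "Less frequently during hospitalization and at every visit to the outpatient clinic hemoglobin, platelets, glucose, creatinin and liver enzymes" are among the values determined.

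**The concern.** Entry and stopping rules for the same hazard should agree: a value that requires the drug to be stopped should also prevent it from being started. Here the entry table applies only the creatinine half of the article's own definition of severe renal dysfunction. Creatinine and eGFR differ systematically by sex and age, so a single creatinine cut-off corresponds to a lower eGFR in women and in older patients.

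The stopping rule does not clearly repair this. It speaks of subjects who develop the condition, and a patient who has it at entry has not literally developed it on study. If the rule is nevertheless read to include her, she meets a discontinuation criterion at her first dose.

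What is at stake is patient safety on a small scale. The abstract names deterioration of renal function and lactic acidosis as safety parameters. Treatment starts within 3 h of PCI and the dose is not adjusted, so the entry and stopping criteria are the main renal safeguards. Screening staff working to that timetable could reasonably take the one stated number as the complete renal test.

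**Working it through.** **The two rules side by side**

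| | Creatinine >177 μmol/L | eGFR <30 |
|---|---|---|
| Entry (Table 2) | yes, pre-PCI | not stated |
| Stopping (Treatment) | yes | yes |

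The plan gives no figure on this point to reproduce. The question is whether creatinine at or below 177 μmol/L is compatible with eGFR below 30.

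**Inputs.** Both thresholds come from the article. It names no eGFR equation, so two common ones are assumed to show the range (Cr in μmol/L, non-Black coefficient):

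- MDRD: eGFR = 175 × (Cr/88.4)^−1.154 × age^−0.203, × 0.742 if female.
- CKD-EPI 2009, in the range where Cr/88.4 exceeds κ: eGFR = 141 × ((Cr/88.4)/κ)^−1.209 × 0.993^age, with κ = 0.7 and a factor of 1.018 for women, κ = 0.9 and no factor for men.

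**Worked example: woman aged 65, creatinine 177 (not excluded).** Cr/88.4 = 2.002.

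- MDRD: 175 × 2.002^−1.154 × 65^−0.203 × 0.742 = 175 × 0.449 × 0.429 × 0.742 ≈ 25.0.
- CKD-EPI: 141 × (2.002/0.7)^−1.209 × 0.993^65 × 1.018 = 141 × 0.281 × 0.633 × 1.018 ≈ 25.5.

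Both values are below 30.

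**eGFR at creatinine 177 μmol/L**

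| Age | Woman, MDRD | Woman, CKD-EPI | Man, MDRD | Man, CKD-EPI |
|---|---|---|---|---|
| 50 | 26.3 | 28.4 | 35.5 | 37.7 |
| 65 | 25.0 | 25.5 | 33.7 | 34.0 |
| 85 | 23.6 | 22.2 | 31.9 | 29.5 |

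**Creatinine (μmol/L) at which eGFR equals 30.** Solving each equation for Cr gives Cr = 177 × (eGFR at 177 / 30)^(1/1.154) for MDRD, and the same with 1/1.209 for CKD-EPI.

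| Age | Woman, MDRD | Woman, CKD-EPI | Man, MDRD | Man, CKD-EPI |
|---|---|---|---|---|
| 50 | 158 | 169 | 205 | 214 |
| 65 | 151 | 155 | 196 | 196 |
| 85 | 144 | 138 | 187 | 175 |

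The uncovered band runs from the tabulated value up to 177. For a woman of 65 it is about 151–177 (MDRD) or 155–177 (CKD-EPI). For men there is no band, except in the very old under CKD-EPI.

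**Age at which creatinine 177 gives exactly eGFR 30.** Women: about 26 (MDRD) or 42 (CKD-EPI). Men: about 83 (CKD-EPI), or no realistic age (MDRD, 114.5). At the entry limit itself, therefore, women above these ages are already past the stopping threshold, while almost no men are.

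**Patients to whom a change could still apply.** The Current status section reports: "As of August 1st, 2012, 266 patients have been randomized". Remaining: 350 − 266 = 84, or 380 − 266 = 114 if recruitment is extended to its cap.

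**The case against.** The strongest reply is that the plan's intent is already clear. The abstract excludes severe renal dysfunction, and the only definition of that term in the article includes eGFR below 30; read together, entry and stopping coincide. Failing that, an investigator who must stop metformin at eGFR below 30 would hardly regard the same value as compatible with starting it, so the contra-indication or judgment exclusion would apply. What counts as a contra-indication may be spelled out in the full protocol. On the stopping side, nobody would keep a patient on drug because her low eGFR predated randomisation, and investigator judgment and repeated creatinine checks give further protection. Finally, no count of affected patients can be given, zero is possible, and an amendment approved late in recruitment would reach few people.

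Much of this stands. The general exclusions may well work in practice, exposure is limited by later monitoring, and reading the word develop strictly is a weak argument by itself. The magnitude in patients is unknown. Inclusion was expected to finish in January 2013 and an amendment takes time, so fewer than the 84 remaining patients would be enrolled under it unless recruitment is extended.

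What does not stand is the claim that the gap is closed. None of these readings puts an eGFR value at entry. The abstract's wording, read with the stopping definition, shows that Table 2 carries out only half of the article's own definition. This is a mismatch between two numeric rules that the article does state, so it cannot be put down to condensation alone.

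**Conclusion.** The concern holds, as a minor point. The stated numeric entry limit admits patients who already meet the article's own stopping threshold, unless a general exclusion is read to cover them. Under either assumed equation this concerns mainly women from middle age onward: at ages 50 to 85 the band starts at 158 down to 144 μmol/L (MDRD) or 169 down to 138 μmol/L (CKD-EPI) and ends at 177. Men are almost unaffected.

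The conclusion that a gap exists does not depend on which of the two equations is used; its exact edges do. How many enrolled patients fall in the band cannot be derived from the article, and calling it very small is a judgment. No sample-size, power or alpha figure changes, and no bias in the intention-to-treat comparison of LVEF is claimed.

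**What to change.** Extend the renal line in Table 2 for patients still to be enrolled, for example: *creatinine above 177 μmol/L or estimated GFR below 30 ml/min per 1.73 m², both from the pre-PCI sample*. Name the eGFR equation, so that entry and stopping are judged on the same scale.

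Optionally, reword the third stopping reason to cover subjects who *have or develop* severe renal dysfunction. This adds little once the entry line is corrected, but it removes any doubt about patients already on treatment.

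The cost is a small amendment during recruitment and possibly a very few additional exclusions. No extra test is needed, because eGFR follows from the pre-PCI creatinine already required, together with age and sex.

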### Study efficacy parameters

The primary efficacy parameter of the GIPS-III trial is LVEF measured by cardiac MRI 4 months after randomization, based on an intention-to-treat analysis. LVEF, is an important predictor of prognosis after MI [36, 37].

A per-protocol analysis, excluding patients diagnosed with new onset diabetes and treated with oral antihyperglyceemic agents or insulin prior to cardiac MRI, will be performed as a secondary efficacy parameter. Other secondary efficacy parameters include major cardiac adverse events (MACE; death, recurrent MI, target lesion revascularization), stroke, non-elective hospitalizations for chest pain or heart failure, all recurrent coronary interventions, and internal cardiac defibrillator implantations. Mortality will be divided into cardiac and non-cardiac. Cardiac death will be divided into three categories: heart failure, sudden death and other. A cardiologist will confirm deaths from cardiovascular causes by examining medical records obtained from hospitals and attending physicians or from the attending general practitioner if the patient died at home. Further, echocardiographic parameters of diastolic function, incidence of new onset diabetes, additional parameters measured by MRI, skin autofluorescence, electrocardiographic parameters, and blood sample analyses, will be used as tertiary efficacy endpoints.

